**Fig. 1 Fig1:**
[figure not shown]
Illustration of the study design, with 4 obligatory data entry points for a complete core data set

The criteria applying for patient enrolment into the registry were kept simple as a result of the low incidence of DC in children and to actively encourage recruitment (Table 1).

**Table 1 Tab1:** Overview of inclusion and exclusion criteria

Inclusion criteria	Exclusion criteria
- Age ≤ 16 years at the time of surgery	- Cranioplasty for conditions other than DC (e.g. congenital skull defects)
- Any type of underlying cerebral insult	
- Informed consent obtained	
- Ability to provide follow-up of at least 24 months after cranioplasty	

Based on retrospective data and an exploratory review of the literature, we estimate an annual recruitment of 2 to 5 patients per centre. The experience of the German Cranioplasty Registry for adult patients (GCRR) has shown that approximately 10 national centres can be expected to participate, depending on the size of the country [22]. Sample size justification is based on a minimal assumption of 20 contributing centres for the ESPN pedCCR, with mean enrolment of 3.5 patients per year. The registry could therefore have an annual recruitment of 70 patients.

Data entry will be web-based and the protocol is optimised towards efficiency and low resource requirements for the contributing centres in order to encourage active and lasting enrolment, complete data entries and sufficient follow-up. A complete minimal data set for a patient surviving after DC would include four data entry points, i.e. forms for DC Module, Cranioplasty Module and two Routine Follow-up Modules at 12 and 24 months after cranioplasty, respectively (Fig. 1). The data elements for each module are partially based on the National Institute of Neurological Disorders and Stroke (NINDS) Common Data Elements (https://commondataelements.ninds.gov). Additionally, several validated scores and measures are explicitly or implicitly contained within the forms. The forms for each module are outlined below:

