## Aims and objectives

After reaching consensus to establish a multicentre, prospective, registry under the auspices of ESPN, an initial international steering committee was formed to formulate the study goals and generate a proposal for a study protocol, which was subsequently ratified by the ESPN board.

The primary objective of this study is a detailed systematic assessment of DC and cranioplasty in children (defined as patients ≤ 16 years of age at the time of surgery) with regard to indication, timing, technique and outcomes, irrespective of underlying disease and with a minimum follow-up of 24 months after cranioplasty. The secondary objective is the comparison of treatment strategies and identification of predictors for optimal outcomes of DC and cranioplasty. This study will generate an international multicentric, prospectively collected data set to achieve these objectives.

Such systematic and high-quality data collection and analysis will improve the evidence base and thus medical care in several specific aspects. The concept of the study is characterised by patient orientation: Based on a large, prospective patient series, we aim for identifying risk factors as well as optimal and suboptimal approaches. This effort may ultimately reduce the complication rate, thereby increasing patient safety and optimizing outcome. The study protocol explicitly includes the long-term course and health-related quality of life (using KIDSCREEN-10) in age-dependent self or external assessment, in addition to the King’s Outcome Scale for Childhood Head Injury (KOSCHI) [35, 36]. The latter scale is validated for TBI, but can be applied to other conditions similar to the Glasgow Outcome Scale.

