### Study design

This is a multicentre, prospective, registry. Patients ≤ 16 years of age at the time of surgery can be included after informed consent as detailed below, irrespective of underlying disease (i.e. indication for DC). In surviving patients, the study centres are committed to contributing data on subsequent cranioplasty as well as a minimum follow-up of 24 months after cranioplasty (Fig. 1). Further follow-up until adolescence or adulthood is encouraged.

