**Fig. 2 Fig2:**
[figure not shown]
Representative screen shots of the pedCCR database — **A** homepage (homepage: www.pedccr.com) and **B** data entry form for DC

Patients will be pseudonymised (consecutive numbers) locally by the respective centre. The central data collection will then be done anonymously, i.e. the central database itself does not contain any identifying patient information and the pseudonymisation key will be securely kept at the local centre.

As this is a prospective registry without a limited study period, data collection will be ongoing and no endpoints were predefined. Regular audits will be performed to ensure data quality and integrity. Data analysis will be performed with descriptive statistics. Based on results from the previous literature, the following statistical assumptions regarding relevant clinical variables were made: 30-day-complication rate after DC — 40%; good outcome after DC — 50%; mortality after DC — 30% and autologous bone flap resorption rate — 80%. With the aim of a confidence level of 90% and an error margin of less than ± 10%, an analysis will be carried out for *N* = 100 included cases. To compare the complication rate between autologous versus allogeneic cranioplasty, an evaluation of *N* = 150 cases per cranioplasty modality will be carried out in view of the complication rates from the literature of 33% versus 14%.

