### Ethics and informed consent

The study will be carried out in accordance with the principles of the Declaration of Helsinki in the revised version of 2013. The study protocol has been approved by the ethical review board at Heinrich-Heine-University, Düsseldorf, Germany (study number 2021–1653). Each centre will need to have obtained a positive local ethics vote before beginning enrolment. The study protocol and consent forms in German and English will be available for download on the study homepage upon user registration. Since we are including underage subjects, the legal representatives or the carer must provide written consent. If the minor is able to understand the nature of the study, his/her written consent is also required. An age-appropriate adapted patient information leaflet and consent form will be provided. The individual patient data can be deleted completely and irretrievably at any time upon the patient’s request, without giving reasons.

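### An inclusion criterion asks for 24 months' follow-up after cranioplasty without limiting it to survivors, which conflicts with the plan to estimate mortality and outcome after DC and risks selection on prognosis

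*Protocol article*

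**What the plan says.** Table 1, in the Study design section of the protocol article, sets out the criteria for enrolling patients. Beside age, type of insult and informed consent, it lists "Ability to provide follow-up of at least 24 months after cranioplasty". The row has no survivor qualifier and does not say how or when it is judged.

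The rest of the article treats the 24 months in two ways:

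- **Limited to survivors.** Study design says "In surviving patients, the study centres are committed to contributing data on subsequent cranioplasty", and the sentence puts the 24-month minimum under the same condition. The same section, describing the forms, says "A complete minimal data set for a patient surviving after DC would include four data entry points".
- **Not limited.** The primary objective under Aims and objectives is worded "irrespective of underlying disease and with a minimum follow-up of 24 months after cranioplasty".

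Data management and statistical analysis then names the quantities to be estimated at N = 100, with 90% confidence and a margin below ±10%. They include "mortality after DC — 30" per cent and good outcome after DC at 50%. The Decompressive craniectomy module records the outcome scale at discharge or day 30 after DC, well before any follow-up of a cranioplasty could begin.

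**The concern.** The row makes entry depend on something that lies two years beyond a second operation. Children who die after DC cannot supply that follow-up, and neither can survivors who never have a cranioplasty. Death after DC is one of the events the registry is sized to measure, so a criterion that can remove it at the door conflicts with the estimation plan.

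A milder reading still leaves a problem. If the row means capability as judged at enrolment, the centre must decide whether this child is likely to complete two years after a later operation. The children most readily judged unable are those with the worst prognosis, and prognosis is tied directly to both mortality and good outcome.

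Three things are at stake:

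- Mortality after DC could read too low and good outcome too high.
- Centres that interpret the row differently could show differences in mortality that come from enrolment. This matters for the secondary objective of comparing treatment strategies.
- Children who were never entered cannot be restored to the denominator in the analysis, and a larger N does not help.

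**Working it through.** **Inputs from the article.** Mortality after DC 30%, good outcome after DC 50%, 30-day complications 40%, bone flap resorption 80%, N = 100, 90% confidence, margin below ±10% (all from Data management and statistical analysis). Good outcome among survivors 60–90% (Introduction).

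**Input assumed.** The share *f* of DC deaths that would be enrolled. The documents give no figure, so the full range from 1 to 0 is shown. All survivors are taken as enrolled.

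**Step 1: the plan's own figure.** The half-width of a two-sided 90% interval is 1.645 × √(p(1 − p)/100).

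| Quantity | p | Half-width (points) |
|---|---|---|
| Complications | 0.40 | 8.06 |
| Good outcome | 0.50 | 8.22 |
| Mortality | 0.30 | 7.54 |
| Resorption | 0.80 | 6.58 |

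All are below 10 points, so N = 100 meets the stated aim. The sample size is not in dispute.

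**Step 2: which denominator the 50% belongs to.** With 30% mortality, 70% survive. A good outcome in 60–90% of survivors gives 0.70 × 0.60 = 42% to 0.70 × 0.90 = 63% of all DC patients. The planning value of 50% lies in that range, so it fits a denominator of all DC patients, including those who die.

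**Step 3: effect of missing deaths.** Per unit of DC patients, those enrolled number 0.7 + 0.3*f*. Then

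- observed mortality = 0.3*f* / (0.7 + 0.3*f*)
- observed good outcome = 0.5 / (0.7 + 0.3*f*)

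| Share of deaths enrolled | Mortality | Shift (points) | Good outcome | Shift (points) |
|---|---|---|---|---|
| 100% | 30.0% | 0 | 50.0% | 0 |
| 75% | 24.3% | −5.7 | 54.1% | +4.1 |
| 50% | 17.6% | −12.4 | 58.8% | +8.8 |
| 25% | 9.7% | −20.3 | 64.5% | +14.5 |
| 0% (literal reading) | 0% | −30.0 | 71.4% | +21.4 |

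**Step 4: when the shift passes the margin.**

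- Mortality, 10 points: 0.3*f* / (0.7 + 0.3*f*) < 0.20 gives 0.24*f* < 0.14, so *f* < 0.58.
- Good outcome, 10 points: 0.5 / (0.7 + 0.3*f*) > 0.60 gives 0.7 + 0.3*f* < 0.833, so *f* < 0.44.
- Mortality against its own half-width of 7.54 points: *f* below about 0.68.

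Survivors who never have a cranioplasty are left out of this calculation. The documents give neither their number nor their outcome, so the direction and size of that effect cannot be stated.

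**The case against.** The best defence is that the article plainly means to enrol children who die. It ties the follow-up commitment to surviving patients, describes the four forms for a survivor, closes the DC module at discharge or day 30, includes a mortality-risk score in that module, and plans a mortality estimate. Table 1 is only an overview, and ability to provide follow-up can be read as a capability at entry that a later death does not breach. The abstract also speaks of follow-up as something centres should commit to, which is close to the repair proposed here.

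Much of this stands. A reader might infer from the row that mortality and outcome will be estimated in survivors only, but the documents do not establish that. A reader might also infer that both estimates must be off by more than ±10 points. That depends on an unknown share: with half the deaths missed, good outcome moves 8.8 points and stays inside the margin.

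Two further inferences should not be drawn. One is that written consent around an emergency operation loses the families of children who die early. The Ethics section requires that "the legal representatives or the carer must provide written consent" but does not say when, and nothing in the article supports the claim about those families. The other is that the article is at fault for not describing consecutive enrolment or a log of patients not entered. A condensed article may leave such detail to the full protocol.

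The defence does not remove the conflict itself. Eligibility is decided from the criteria, and the row there carries no survivor limit. The primary objective lacks one too. The survivor wording in Study design presupposes a cranioplasty, so no text covers survivors who never have one. The capability reading still invites a judgement of prognosis at entry.

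**Conclusion.** The point holds as an inconsistency that creates a risk of selection. Table 1 applies to all patients a requirement that the Study design text applies only to survivors and that, taken literally, would make the planned mortality estimate 0% by construction.

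The size depends on how centres apply the row. The shift passes 10 points for mortality only if more than about 42% of deaths go unenrolled, and for good outcome only if more than about 56% do. These thresholds rest on the article's 30% and 50%, on 50% referring to all DC patients, and on full enrolment of survivors. If centres already read the row as the Study design text suggests, and do not select on prognosis, there is no bias from this source.

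It is still worth correcting before enrolment builds up, because mortality is a named target and the correction is a matter of wording.

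**What to change.** 1. Remove the row from the patient inclusion criteria. Restate it as a centre commitment to follow surviving patients who undergo cranioplasty for at least 24 months afterwards.
2. State that every DC patient aged 16 or under at surgery, with consent, is eligible regardless of prognosis, later survival or later cranioplasty.
3. State that all enrolled DC patients form the denominator for mortality and outcome after DC.
4. Align the wording of the primary objective, so that the 24 months apply to survivors with a cranioplasty.

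N = 100 is unchanged: with all DC patients enrolled, the planned precision is 30% ± 7.5 points for mortality and 50% ± 8.2 points for good outcome. The cost is a short amendment (one row of Table 1 and the matching sentences) with ethics notification. Some enrolled patients will have fewer than four data entry points, which the survivor wording in Study design already implies.

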### Decompressive craniectomy module

48 itemsPaediatric GCS prior to DC and at discharge or day 30 after DC [41]Paediatric Risk of Mortality Score (PRISM) within 4 h after admission [42]Rotterdam CT Score [43]KOSCHI at discharge or day 30 after DC [35]

### Cranioplasty module

26 itemsPaediatric GCS prior to cranioplasty and at discharge or day 30 after cranioplastyKOSCHI prior to cranioplasty and at discharge or day 30 after cranioplastyKIDSCREEN-10 prior to cranioplasty [36]

### Routine follow-up module

10 itemsPaediatric GCSKOSCHIKIDSCREEN-10Oulo Resorption Score (if bone flap resorption observed on imaging) [44]

### Incident reporting module

13 itemsPaediatric GCSKOSCHIKIDSCREEN-10Oulo Resorption Score (if bone flap resorption observed on imaging)

### Data management and statistical analysis

A web-based database using Filemaker^®^ software has been designed to allow password-protected data entry (Fig. 2), similar to the system successfully used for the TROPHY registry [45, 46]. The central server is physically located and professionally hosted in Europe. Data transfer between the user and the study server is encrypted (SSL coding) to assure data privacy. Access to the online registry application is provided via the study homepage: www.pedccr.com.

**Fig. 2 Fig2:**
[figure not shown]
Representative screen shots of the pedCCR database — **A** homepage (homepage: www.pedccr.com) and **B** data entry form for DC

Patients will be pseudonymised (consecutive numbers) locally by the respective centre. The central data collection will then be done anonymously, i.e. the central database itself does not contain any identifying patient information and the pseudonymisation key will be securely kept at the local centre.

As this is a prospective registry without a limited study period, data collection will be ongoing and no endpoints were predefined. Regular audits will be performed to ensure data quality and integrity. Data analysis will be performed with descriptive statistics. Based on results from the previous literature, the following statistical assumptions regarding relevant clinical variables were made: 30-day-complication rate after DC — 40%; good outcome after DC — 50%; mortality after DC — 30% and autologous bone flap resorption rate — 80%. With the aim of a confidence level of 90% and an error margin of less than ± 10%, an analysis will be carried out for *N* = 100 included cases. To compare the complication rate between autologous versus allogeneic cranioplasty, an evaluation of *N* = 150 cases per cranioplasty modality will be carried out in view of the complication rates from the literature of 33% versus 14%.

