**Conclusion:**

The registry aims to define predictors for optimal medical care and patient-centred treatment outcomes. The ultimate goal of the registry is to generate results that are so relevant to be directly transferred into clinical practice to enhance treatment protocols.

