A systematic analysis and comparison of different cranioplasty materials and techniques will deliver further knowledge in order to optimise quality of care and cost-effectiveness in this critical phase after TBI, as cranioplasty carries significant short- and long-term risks in children [34]. Ultimately, based on the data collected, revision surgery could be avoided and implants with the best cost–benefit ratio could be identified. Additionally, the optimal timing of cranioplasty will be analysed, as there is currently conflicting data on early versus delayed cranial reconstruction [37–40]. A further strength of the registry is its focus on specific technical details from a paediatric neurosurgical perspective, which are often impossible to be reconstructed retrospectively from operation notes.

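### The stated method, descriptive statistics, does not fit the secondary objective: comparisons of non-randomised treatments are left unadjusted and open to confounding by indication and centre

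*Protocol article*

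**What the plan says.** The method is given in the section on data management and statistical analysis, without qualification: "Data analysis will be performed with descriptive statistics". The same paragraph says that no endpoints were predefined. It then sets out two evaluations: estimates of single rates at 100 cases, and a two-group contrast introduced with "To compare the complication rate between autologous versus allogeneic cranioplasty", for which an evaluation of "150 cases per cranioplasty modality will be carried out" on literature complication rates of 33% v 14%.

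The aims go beyond description. Under Aims and objectives: "The secondary objective is the comparison of treatment strategies and identification of predictors for optimal outcomes of DC and cranioplasty". The same section adds "we aim for identifying risk factors as well as optimal and suboptimal approaches", promises "A systematic analysis and comparison of different cranioplasty materials and techniques", and says that "the optimal timing of cranioplasty will be analysed". The abstract's conclusion repeats the predictor aim: "The registry aims to define predictors for optimal medical care and patient-centred treatment outcomes".

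Study design and Table 1 describe a prospective multicentre registry without random allocation, open to any underlying cerebral insult up to age 16. The article mentions no regression, stratification, weighting or centre effect. Its Conclusions nevertheless expect high internal validity.

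**The concern.** Crude rates describe the children who received each material. They do not separate the effect of the material from differences between those children, and they do not separate one predictor from others correlated with it. In a registry with mixed indications, age, type of insult, severity, timing and centre may all differ between the material groups. The Introduction itself notes relevant anatomical and physiological differences within the paediatric age range.

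The abstract wants results that can be carried straight into practice. A crude difference in complication rates between materials would probably be read as an effect of the material, and likewise for early v delayed cranioplasty. More patients would narrow the interval but would not remove the bias.

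**Working it through.** **1. The article's own figures**

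*Single rates, N = 100, 90% confidence.* Half-width = 1.645 × √(p(1−p)/100). This gives 8.1 points at 40%, 8.2 at 50%, 7.5 at 30% and 6.6 at 80%. All are below 10 points, so the descriptive target is met.

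*Material contrast, 150 per modality, 33% v 14%.* The article states no significance level, sidedness or power, so 150 has no single reproduction. At an assumed two-sided 5%, with p̄ = 0.235:
- null standard error √(2 × 0.235 × 0.765/150) = 0.0490
- alternative standard error √((0.33 × 0.67 + 0.14 × 0.86)/150) = 0.0477
- power = Φ((0.19 − 1.96 × 0.0490)/0.0477) = 97.6%

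The same formula needs 77 per group for 80% power and 103 for 90%. The number is ample for a crude contrast, so the weakness is bias and not size.

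**2. What confounding could do (all inputs assumed)**

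Suppose material has no effect and one binary risk factor is unevenly spread. Crude rate = q × r₁ + (1−q) × r₀, where q is its prevalence in the group and r₁, r₀ are the risks with and without it. For the case in the first row:
- 0.6 × 0.35 + 0.4 × 0.14 = 26.6%
- 0.2 × 0.35 + 0.8 × 0.14 = 18.2%

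The last column is the chance that a crude two-sided 5% test at 150 per group is significant.

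| Prevalence | Risks with v without | Crude rates | Difference | Significant |
|---|---|---|---|---|
| 60% v 20% | 35% v 14% | 26.6% v 18.2% | 8.4 points | 41% |
| 60% v 40% | 35% v 15% | 27% v 23% | 4 points | 13% |
| 70% v 30% | 40% v 10% | 31% v 19% | 12 points | 67% |
| 80% v 20% | 40% v 10% | 34% v 16% | 18 points | 95% |

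The direction is arbitrary. The opposite imbalance would hide a true difference.

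**3. Room to adjust**

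Expected events: 150 × 0.33 + 150 × 0.14 = 49.5 + 21 = 70.5, or about 7 parameters at 10 events each.

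If covariates explain a share R² of the variance in material choice (assumed), the effective size is about 150 × (1−R²):
- R² 10%: 135 per group, power 96%
- R² 30%: 105 per group, power 91%
- R² 50%: 75 per group, power 79%

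**4. Centre (20 centres from Study design; ICC 0.01, 0.05, 0.10 assumed)**

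- *Rate in one group*, 150/20 = 7.5 cases per centre: variance factor 1 + 6.5 × ICC = 1.07, 1.33, 1.65.
- *Contrast, both materials used equally in every centre*: the shared centre effect cancels and the factor is about 1 − ICC = 0.99, 0.95, 0.90.
- *Contrast, material chosen wholly by centre*, 300/20 = 15 per centre: factor 1 + 14 × ICC = 1.14, 1.70, 2.40. Power falls to about 96%, 85%, 71%.

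The effect of centre on the contrast therefore depends on how material use is spread across centres, which the article does not say.

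**The case against.** The strongest reply is that this is a condensed article. It says a study protocol can be downloaded from the homepage after registration, and covariates, model form and the handling of centre are commonly left to such a document. The article also does not say that description is the only method, description can be stratified, and a sized comparison follows shortly after. The registry is open-ended, and its primary objective suits description.

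Much of this stands. The absence of model detail is no fault in itself, and adjustment can still be specified before the comparison is run. The mismatch remains: the article names a method without qualification, and that method does not serve an objective it also states. A fuller plan with models would have to depart from this sentence.

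A reader might also infer four stronger things that the documents do not support:

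- *That the results will be confounded, or that most of the 33% v 14% gap is artefact.* What drives the choice of material is not described, and those rates are literature values used for sizing. Only openness to confounding can be claimed.
- *That ignoring centre makes the intervals too narrow.* This holds for single-group rates. For the contrast it holds only if material choice largely follows centre.
- *That a child whose autologous flap is replaced by an implant is counted in both groups.* The article does not define a case for this comparison. The minimal data set has one cranioplasty form per surviving child, and where revisions are recorded is not stated. Double counting is possible but not shown.
- *That every desirable covariate is already held.* Prior infection, for example, is not shown as an item.

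**Conclusion.** The point holds as a mismatch between the stated method and the secondary objective, together with the planned comparisons of materials and timing. Followed as written, the plan gives an unadjusted contrast between materials and no means of isolating predictors. The primary objective and the estimates at 100 cases are not affected.

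The size of any bias cannot be derived from the documents. Under the assumed imbalances, a null material effect shows as a crude difference of 4 to 18 points, against the 19 points used for planning. These figures show what is possible and do not predict what the registry will find. The finding that adjustment is affordable rests on the article's 33% and 14%, an assumed two-sided 5% test and the assumed R² values.

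**What to change.** Replace the single method sentence with a statement by objective:

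- **Primary objective:** descriptive statistics, as now.
- **Secondary objective and the comparison at 150 per modality:** an adjusted analysis, by regression or propensity-score weighting, with centre accounted for (a random effect or cluster-robust standard errors).
- **Covariates:** a short prespecified set from items already collected, such as age, type of insult, paediatric GCS or KOSCHI before cranioplasty, and the interval from DC to cranioplasty. The Cranioplasty Module lists both scores, the abstract says indication and timing are collected, and age is an eligibility criterion. The DC Module also offers PRISM and the Rotterdam CT score. About 70 events set the limit on the number of parameters.
- **Unit of analysis:** each child counts once, by the material of the first cranioplasty.
- **Reporting:** results described as associations.

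If the sponsor prefers not to adjust, the alternative is to label the comparisons exploratory and limit the objective to description.

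The cost is protocol or SAP wording and modest extra analysis, with no extra patients. Adjusted intervals will be somewhat wider than crude ones. The change should be made before the comparison is run.

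### The N = 100 analysis secures its ±10-point margin for the craniectomy-level rates but not for autologous bone flap resorption, which has a smaller and later denominator

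*Protocol article*

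**What the plan says.** The section Data management and statistical analysis lists four assumed rates from the literature. Two are given as "30-day-complication rate after DC — 40%; good outcome after DC — 50" per cent, and two as "mortality after DC — 30% and autologous bone flap resorption rate — 80" per cent. One precision statement then covers all four. Its target is put as "With the aim of a confidence level of 90% and an error margin of less than" ten points either way. The analysis set for all four rates is the first hundred children counted as included, with no further condition. The next sentence plans a separate comparison of autologous with allogeneic cranioplasty and counts 150 cases per modality.

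Study design gives the recruitment assumptions. Per centre, "we estimate an annual recruitment of 2 to 5 patients per centre"; with 20 centres at a mean of 3.5, "The registry could therefore have an annual recruitment of 70 patients". It limits cranioplasty data to surviving patients and places the routine follow-up forms at 12 and 24 months after cranioplasty. The resorption score sits on those forms and on the incident form. Under Aims and objectives, the primary objective assesses outcomes "with a minimum follow-up of 24 months after cranioplasty".

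**The concern.** Three of the four rates describe what happens after DC, so every included child can contribute. The fourth does not. A flap can resorb only in a child who survives, receives autologous bone and is then observed. The plan assumes 30% mortality and expects allogeneic cranioplasty, but carries neither into the resorption denominator. It also counts cases at inclusion, which Study design uses in the sense of enrolment after consent, while resorption is documented a year or more after a second operation.

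The Introduction names resorption as a leading problem of paediatric cranioplasty. A resorption figure reported at 100 inclusions could carry a precision claim that its actual denominator does not support, and could rest on immature follow-up.

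**Working it through.** **Inputs from the Protocol article.** Confidence 90% (two-sided z = 1.645); target half-width below 10 points; N = 100; rates 40%, 50%, 30% and 80%; mortality 30%; recruitment 70 per year (40 to 100 per year for 20 centres at 2 to 5 each); forms at 12 and 24 months after cranioplasty.

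**Inputs not given, so assumed with a range.** Autologous share among survivors (30 to 100%), interval from DC to cranioplasty (0 to 6 months), loss to follow-up (0 to 20%).

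**1. The plan's own figure.** Half-width = z × √(p(1 − p)/n), with n = 100:

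- p = 0.40: 1.645 × √(0.24/100) = ±8.1 points
- p = 0.50: 1.645 × √(0.25/100) = ±8.2
- p = 0.30: 1.645 × √(0.21/100) = ±7.5
- p = 0.80: 1.645 × √(0.16/100) = ±6.6

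All four meet the target if all 100 children are evaluable. The arithmetic is right on that premise.

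**2. Number needed for resorption.** n = z² × p(1 − p)/0.10² = 2.706 × 0.16/0.01 = 43.3, so 44 evaluable autologous cases.

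**3. Number available from 100 inclusions.** Survivors: 100 × 0.70 = 70. With no loss to follow-up:

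| Autologous share (assumed) | Evaluable n | 90% half-width (points) | Inclusions needed for 44 |
|---|---|---|---|
| 100% | 70 | ±7.9 | 63 |
| 70% | 49 | ±9.4 | 90 |
| 60% | 42 | ±10.15 | 105 |
| 50% | 35 | ±11.1 | 126 |
| 40% | 28 | ±12.4 | 158 |
| 30% | 21 | ±14.4 | 210 |

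The last column is 44/(0.70 × share), rounded up. The break-even share is 43.3/70 = 62%, or 44/70 = 63% in whole children. With 20% loss, 56 survivors remain and break-even is 43.3/56 = 77% (44/56 = 79%). A 50% share with 20% loss leaves 28 children and ±12.4.

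**4. Timing, if the analysis is run at the 100th inclusion.** 100/70 × 12 = 17.1 months. This is below 24, so no child can have 24-month data, even with no interval between DC and cranioplasty. Inclusions with 12-month data number (17.1 − 12 − interval) × 70/12:

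- interval 0: 30 inclusions, 21 survivors, ±14.4 even if all are autologous
- interval 3 months: 12.5 inclusions, about 9 survivors, ±22
- interval 6 months: none

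At 100 per year the 100th inclusion falls at month 12 and none has 12-month data. At 40 per year it falls at month 30. Then 20, 10 or 0 inclusions, before deaths, could have 24-month data for an interval of 0, 3 or 6 months.

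**The case against.** The strongest reply is that the arithmetic is correct and that failure depends on facts the article does not give. Much of this stands.

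- A reader might infer that 100 inclusions cannot give the margin for resorption. The document does not support that. Mortality alone leaves 70 children and ±7.9, and the denominator fails only below an autologous share of about 63%.
- A reader might infer that the analysis is certain to take place with no 24-month data. The text does not fix the date. If the 100 cases are analysed after follow-up is complete, the timing problem disappears. At 40 per year a few children could have 24-month data anyway.
- The 80% is not tied to 24 months, incident forms can record earlier resorption, and no time course is given. The size of any underestimate at an early cut therefore cannot be stated.
- The planned evaluation at 150 cases per modality would give resorption about ±5.4 (1.645 × √(0.16/150)), and the registry is open-ended. Precision is postponed, not lost.
- A reader might also infer that good outcome should be counted among the 70 survivors only. The Introduction gives 60 to 90% good outcome among survivors. With 70% surviving, that is 42 to 63% of all children, so the assumed 50% fits all DC cases.
- Choosing 90% confidence, or an N above the minimum, is legitimate in a descriptive registry.

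A condensed article may also leave data-cut details to the full protocol. But this article itself states the N, the margin and the rates together, and for one rate they rest on a denominator that cannot apply. The next sentence counts cases per modality, so a suitable denominator was available.

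**Conclusion.** The concern holds in limited form. For 30-day complications, good outcome and mortality, 100 included cases meet the stated target. For autologous flap resorption the target is not secured, because the count is of inclusions and the rate needs at least 44 surviving, autologous, followed-up children. The shortfall is conditional. It arises if the autologous share is below about 63% with no loss, or if the analysis is run at the 100th inclusion at the planned 70 per year. At an assumed even split the half-width is ±11.1, a modest miss. At an analysis at month 17 it is ±14 or wider on 12-month data, with no 24-month data at all.

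The figure of 44 rests on the assumed 80% rate and the normal approximation. This should be corrected before the first analysis, but it does not undermine the registry or its other three estimates.

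**What to change.** Split the precision statement in two.

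1. **DC-level rates.** Keep N = 100, defined as cases with completed 30-day or discharge status, for complications, outcome and mortality.
2. **Resorption.** Trigger this estimate separately, once at least 44 surviving autologous cases have reached the required follow-up form (24 months after cranioplasty, in line with the primary objective). Report any earlier resorption figure by time since cranioplasty, with its actual n and confidence interval and without the ±10-point claim.

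The change is to wording only; data collection stays as it is. The cost is a later resorption result. At 70 per year, with an assumed 3-month interval from DC to cranioplasty and no loss, a 100% autologous share needs 63 inclusions: 63/70 × 12 + 3 + 24 = about 38 months. A 50% share needs 126: 126/70 × 12 + 3 + 24 = about 49 months. Loss to follow-up or a lower share would lengthen this.
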